## Methods/Design

### Main outcome measure

The primary outcome for this trial is PPD, as diagnosed by the Structured Clinical Interview for DSM-IV (SCID-I), administered at 12 weeks post-randomisation (that is immediately post-treatment for mothers in the intervention group).

### Intervention groups

#### Control group

Standard postpartum care as provided to all mothers, including community PPD services.

#### Treatment group

Standard postpartum care as provided to all mothers in addition to 12 weekly sessions of telephone-based IPT.

### Randomization procedure

Randomization is centrally controlled using a web-based randomization service, with stratification based on self-reported history of depression and province. This randomization service was successfully used by [name] in the PPD prevention trial [110]. Provincial stratification is planned, because postpartum care is based on practice standards set by a province’s Ministry of Health. As such, ‘standard postpartum care’ will be very different for each province.

### Outcome measures

#### Primary outcome

##### Postpartum depression

The primary outcome for this trial is PPD, as diagnosed by the Structured Clinical Interview for DSM-IV (SCID-I) [111] administered at 12 weeks post-randomization (Table 1). The SCID-I is a semi-structured interview that includes an introductory overview followed by nine modules, seven of which represent the major DSM diagnostic classes. Because of its modular construction, the SCID-I can be adapted for use in studies in which particular diagnoses (for example, depression only) are of interest. As such, for this trial, the Current Major Depressive Episode (MDE) section of Module A will be used to indicate the presence of a major depressive episode and the Melancholic Features, Atypical Features, and Current Manic Episode sections of Module A will be used to further evaluate the severity of a potential participant’s mood episode(s) and the impact of these subcategories on a participant’s response to the IPT intervention.

**Table 1 T1:** Timing of measurements

**Time**	**Outcome measures**
Baseline	(1) SCID-I, (2) EPDS, (3) STAI-State Anxiety Inventory, (4) Dyadic Adjustment Scale, (5) Experiences in Close Relationships-Revised, and (6) demographic variables
12 weeks post-randomization	(1) SCID-I, (2) EPDS, (3) STAI-State Anxiety Inventory, (4) Dyadic Adjustment Scale, (5) Experiences in Close Relationships-Revised, (6) Maternal Health Service Utilization and Cost of Care Questionnaire, (7) Maternal Satisfaction with IPT Questionnaire (to be completed by mothers in the intervention group), and (8) IPT Activity Log (to be submitted to the Data Coordinating Center by the IPT nurse)
24 weeks post-randomization	(1) SCID-I, (2) EPDS, (3) STAI-State Anxiety Inventory, (4) Dyadic Adjustment Scale, (5) Experiences in Close Relationships-Revised, and (6) Maternal Health Service Utilization and Cost of Care Questionnaire
36 weeks post-randomization	(1) SCID-I, (2) EPDS, (3) STAI-State Anxiety Inventory, (4) Dyadic Adjustment Scale, (5) Experiences in Close Relationships-Revised, and (6) Maternal Health Service Utilization and Cost of Care Questionnaire
Continuous	Nurse IPT Experience Questionnaire (to be completed either at the end of the trial or when an IPT nurse discontinues trial participation)

There are more than 500 reports of published studies using the SCID-I as a diagnostic instrument and the reliability and validity has been extensively reported in diverse studies and samples [112]. In particular, research evaluating the SCID-I has found the measure to yield highly reliable diagnoses for most disorders [112,113], with inter-rater reliability often exceeding 81 % for diagnoses such as major depression [114]. The SCID-I has also been effectively used with postpartum women to assess depression [115-120]. The SCID training materials, for both clinicians and research personnel, include a user’s guide and eight videotapes. At the UCLA Research Center for Major Mental Illnesses, a training and quality assurance program was used to evaluate SCID inter-rater reliability and diagnostic accuracy. Both clinically experienced interviewers and recently trained neophyte interviewers were able to achieve and maintain high levels of inter-rater reliability, diagnostic accuracy, and interviewer skill; at the first quality assurance check after training, there were no significant differences between experienced and neophyte interviewers in inter-rater reliability or diagnostic accuracy [121].

The SCID-I is also administered at 24 and 36 weeks post-randomization, as a secondary outcome. While some attrition of the sample is expected by this time, the additional information will provide important evidence of longer-term effects of the IPT intervention.

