##### Nurse IPT activities

All intervention activities (for example, telephone discussions, left messages, missed sessions) are documented by the IPT nurses using the IPT Activity Log. IPT nurses are requested to return the activity log for a mother immediately post-treatment. This activity log is similar to ones used in [name]’ previous telephone-based trials [103,130], including the PPD prevention trial [110].

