Given that (1) all the preceding studies used self-report measure to assess recovery (for example, no depressive symptomatology using a specific cutoff score) instead of a diagnostic interview such as the SCID, and (2) the proposed trial’s sample will be heterogeneous and include rural and urban mothers from diverse provinces, for the purpose of calculating the sample size, we have made the conservative assumption that 30 % of mothers in the control group will spontaneously recover and will not have major depression at the 12 week post-randomization assessment (70 % will remain clinically depressed) (Table 2). The sample size is based on the ability to detect a moderate decrease of 20 percentage points to a rate of 50 % among mothers in the intervention group. Our partners in the participating public health departments agree that a 20 % absolute decrease in the number of mothers with depression post-treatment is the minimum effect that would be considered clinically meaningful, warranting the time and effort to develop and implement an IPT program. A two-tailed α error of 0.05 was chosen, as there is insufficient empirical evidence of either risk or benefit associated with the proposed telephone-based IPT intervention. Thus, with 80 % power, a two-tailed α error of 0.05, and using a test of two independent proportions to find a 20 % reduction in the number of mothers with depression at 12 weeks post-randomization (immediately post-treatment for mothers in the intervention group), a sample size of 188 (94 per group) is required; we plan to enroll 240 to allow for up to 20 % loss to follow-up. This sample size also provides power to detect a 20 % absolute reduction in other secondary outcomes, such as anxiety.

**Table 2 T2:** Sample size differences between groups

**Control group depression rate**	**IPT group depression rate**	**Size per group**
75	55	88
70	50	94
5	45	96

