### Operational details

#### Telephone-IPT intervention

Mothers allocated to the treatment group receive 12 weekly IPT sessions, each session 50 to 60 min in duration and delivered over the telephone by a trained IPT nurse who receives weekly supervision by an IPT trainer ([name]). Within 72 h, the IPT nurse will either administer session 1 (if possible) or at least make an initial call to the participant to schedule session 1 (to occur within the week following enrolment). The scheduling of IPT sessions are based on mutual availability between the mother and IPT nurse. IPT is administered according to the standardized manual by Stuart and Robertson [56,140], with some modifications to accommodate the postpartum context of depression. These modifications are based on previous IPT trials for PPD [141].

As conducted in standard IPT clinical practice, a minority of trial participants identified as either in acute crisis at the end of treatment, or who are progressing however remain significantly symptomatic, thus would benefit from extending the course, may be offered up to four additional IPT sessions (that is, conduct 12 or a maximum of 16 sessions per trial participant, as appropriate). A full course of therapy must be completed within 16 weeks to account for any additional sessions and/or occasional scheduling conflicts or difficulties.

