#### Compliance

It is expected that 80 % of the intervention group will receive IPT due to the specific inclusion/exclusion criteria, informed consent procedures, and intervention compliance procedures. Some of the participants will drop out because of their preference for in-person therapy, scheduling difficulties, unsuccessful contact post-randomization or due to crises that can in some cases require contact with child protection service agencies, public health and/or their family physicians. In this trial, treatment compliance means the completion of at least 10 IPT sessions. Monitoring compliance of the intervention are three-fold: (1) IPT nurses’ completion of IPT Activity Logs for each participant, (2) supervision of the IPT intervention as provided by [name] and [name], and (3) mothers’ evaluations of their IPT experiences.

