#### Comparators and time horizon

The alternatives in the trial are telephone IPT vs. standard postpartum care of mothers with PPD. Given that IPT in this context is adjunctive, the economic analysis will retain a high degree of external validity. The economic component of the study will measure costs from randomization to 36 weeks post-randomization. We recognize that the resource implications of the trial intervention will probably extend beyond that point. As the incidence of affective symptoms gradually decreases, however, the longer-term cost differences between programs are also likely to decrease. Moreover, the costs of implementing the intervention itself will be fully captured. The measured cost-effectiveness will therefore be a conservative estimate. Decision analytic modeling of longer-term outcomes beyond 36 weeks will be undertaken in secondary analyses if there are still differences between groups in resource utilization and costs at the end of trial data collection.

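### Table 1 dates the IPT Activity Log and the satisfaction questionnaire at 12 weeks although therapy may run to 16: the log has two conflicting due dates, and some mothers would rate unfinished therapy

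*Protocol article*

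**What the plan says.** All references are to the protocol article.

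- **Table 1 (Timing of measurements), 12-week row.** It lists the Maternal Satisfaction with IPT Questionnaire as item 7, followed by "8) IPT Activity Log (to be submitted to the Data Coordinating Center by the IPT nurse".
- **Nurse IPT activities, repeated under Post-randomization data.** All intervention activities are documented, and "IPT nurses are requested to return the activity log for a mother immediately post-treatment".
- **Maternal evaluation of IPT.** The satisfaction questionnaire is assessed at 12 weeks post-randomization, as in Table 1.
- **Telephone-IPT intervention.** The course is 12 weekly sessions. A minority who are in acute crisis at the end of treatment, or who are improving but still clearly symptomatic, may be offered up to four more. "A full course of therapy must be completed within 16 weeks to account for any additional sessions and/or occasional scheduling conflicts or difficulties". The Abstract also gives a range of 12 to 16 weeks.
- **Compliance.** Here "treatment compliance means the completion of at least 10 IPT sessions", with no week attached. Compliance is monitored through the logs, supervision and the mothers' evaluations.
- **Comparators and time horizon; Measurement of resource utilization.** Costs run to 36 weeks, resource use comes from the nurses' logs, and the article says that "the costs of implementing the intervention itself will be fully captured".
- **Statistical analysis plan, Primary analysis.** The number of sessions will be related to PPD and the other outcomes to look for a dose response.

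**The concern.** A 12-week due date fits a 12-week course but not one that lasts up to 16 weeks. The two items are affected differently.

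For the log, Table 1 and the text agree only when therapy ends by week 12. For a longer course a nurse cannot follow both, and the article neither says which prevails nor provides for a second submission. The log supplies the session count, the compliance status and the nurse time in the economic evaluation. A log closed at week 12 would be incomplete for the mothers with long courses.

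For the questionnaire there is no competing instruction. A mother treated in weeks 13 to 16 would be asked to evaluate therapy she has not finished. Mothers' evaluations of IPT are one of the article's other research questions and one of its three compliance checks.

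The dose-response analysis is affected as well. Sessions after the 12-week SCID cannot influence its result, and the extra sessions go to mothers who are still symptomatic or in crisis. If total sessions were used as the dose for the 12-week outcome, more sessions could appear to go with more depression for that reason alone.

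**Working it through.** **The plan's own figure.** The article computes nothing on this point. Its one calculation is the sample size, "with 80 % power, a two-tailed α error of 0.05", for depression rates of 70 % and 50 %. With pooled variance and no continuity correction:

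n = [1.96·√(2·0.6·0.4) + 0.842·√(0.7·0.3 + 0.5·0.5)]² / 0.20² = 93 per group, against 94 stated.

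Allowing for 20 % loss, 188 / 0.8 = 235, against 240 planned. The figure reproduces and does not depend on the timing question.

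**The log instructions side by side.**

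| Course ends | Due under Table 1 | Due under the two text sections | Agree? |
|---|---|---|---|
| by week 12 | week 12 | end of treatment | yes, in substance |
| weeks 13 to 16 | week 12 | end of treatment, weeks 13 to 16 | no |

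**What a week-12 log would miss.** This assumes that recording stops when the log is submitted, which the article does not say. Session 1 falls between day 0 and the end of week 1 (Telephone-IPT intervention), so with weekly sessions session k falls at week s + (k − 1), where s is 0 to 1.

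- Session 10: week 9 to 10.
- Session 12: week 11 to 12.
- Session 16: week 15 to 16.
- Sessions done by week 12: 12 to 13.

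A 16-session course would therefore lose 16 − 13 = 3 to 16 − 12 = 4 sessions, that is 3/16 = 19 % to 4/16 = 25 %. This mother reached 10 sessions by week 10 at the latest, so her compliance status is right under either due date.

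**A slowed course.** Assume 12 sessions spread evenly up to week 16.

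- Gap between sessions: (16 − s)/11 = 1.36 to 1.45 weeks.
- Session 9: week 11.6 to 11.9.
- Session 10: week 13.1 to 13.3.

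By week 12 she has 9 sessions, and 3 of 12 (25 %) are still to come. A week-12 log would class her as non-compliant; the complete log would class her as compliant. This is the only kind of course for which the 10-session rule could give a wrong answer.

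**Under the text's rule.** If the log is returned when treatment ends, no sessions are lost.

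**The questionnaire.** Table 1 and Maternal evaluation of IPT give the same date. Reconciling the two log instructions would leave it unchanged, so it stays out of line with the 16-week window.

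**The case against.** The best defence is that the log is already handled. Two sections say that all activities are recorded and that the log comes back when treatment ends. The article uses 12 weeks as shorthand for the end of treatment throughout, so the Table 1 row probably condenses that rule. Table 1 speaks of submission and sets no end to recording. The compliance rule has no week-12 limit, and costs run to 36 weeks. Much of this stands. A reader might infer from Table 1 that dose, the compliance rate and the intervention cost are in fact cut short. The documents do not support that: the loss follows only if Table 1 is taken as the operative instruction.

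A reader might also infer that sessions missing from a log could not be recovered. That is not supported either, because all sessions are audio-taped and nurses have weekly supervision. Nor would sessions lost translate one for one into intervention cost, which also includes recruiting, training and supervising nurses.

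It is fair to add that extra sessions are for a minority, that scheduling conflicts are called occasional, and that the questionnaire belongs to the other outcomes and cannot count sessions.

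Two things survive. Table 1 is the measurement schedule, so staff may work from it, and for a course past week 12 it contradicts the text. The questionnaire date is fixed in both places and nothing corrects it.

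**Conclusion.** The point holds as a minor inconsistency with two parts. The log has two due dates that cannot both be met for courses running past week 12. Data would be lost only if Table 1 were followed and recording stopped at submission; in that case a 16-session weekly course loses 3 to 4 sessions, and compliance is misjudged only for slowed courses. The questionnaire is certainly mistimed for any mother still in therapy at week 12.

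The article does not give the number of such mothers or the rate of missed weeks, so no trial-level effect on the mean dose, the compliance rate or the cost can be computed. The primary comparison and the sample size are unaffected.

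**What to change.** - In Table 1, make the log due after each mother's last IPT session, in line with Nurse IPT activities and Post-randomization data.
- In Table 1 and in Maternal evaluation of IPT, move the satisfaction questionnaire to after the last session.
- State that total sessions are used for the compliance rule and the cost, and that sessions delivered before the 12-week SCID are the exposure in the dose-response analysis of the 12-week outcome.
- If any log was submitted before therapy ended, obtain the remaining entries from the IPT nurse. With 212 of 240 participants already enrolled at the reported date, this is best checked now.

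The cost is a few lines of text and possibly a short query to nurses, with no extra participants or visits. The one drawback is that the satisfaction interview will fall at slightly different weeks across mothers.

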#### Secondary outcomes

##### Depressive symptomatology

This outcome is measured using the Edinburgh Postnatal Depression Scale (EPDS) [122], a 10-item self-report instrument. Items are rated on a 4-point scale to produce a summative score ranging from 0 to 30, with higher scores indicating lower maternal mood. This instrument does not diagnosis PPD but rather it is the most frequently used instrument to assess for postpartum depressive symptomatology [16]. Of the 30 PPD treatment studies found in the extant literature [43,123], 83 % (*n* = 25) used a self-report measure to evaluate whether the intervention was effective. Of these 25 studies, 18 (72 %) incorporated the EPDS. Created to counter the limitations of other well-established depression scales, it has been validated by standardized psychiatric interviews with large samples and has well-documented reliability and validity in over 11 languages [14]. The published recommended EPDS cutoff score of > 12 [122] is used to examine depressive symptomatology at 12, 24, and 36 weeks post-randomization.

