#### Self-referrals

Women who are between 2 and 24 weeks postpartum and self-identify as feeling down or depressed may also self-refer to the trial.

All referred mothers are contacted by the trial coordinator and provided a detailed explanation of the study. If the mother expresses interest in participating in the trial, she is further assessed for eligibility. Eligible women are asked to provide verbal consent to participate in the study; if she consents, baseline information is collected by the trial coordinator. Using a web-based, centrally controlled randomization service, the mother is randomized to either the control (standard postpartum care) or intervention group (standard postpartum care plus 12 telephone-IPT sessions), with stratification based on province and self-reported history of depression. Following randomization, participants are immediately informed of their study group assignment.

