### Statistical analysis plan

#### Primary analysis

Data will be analyzed using SAS software and an intent-to-treat approach will be used. Every effort will be made to collect follow-up data from all participants. We will not impute a score for missing primary outcome data. A two-sided significance level of 0.05 will be used for the primary outcome; a significance level of 0.01 (two-sided) will be used for secondary and other outcomes to account for multiple comparisons. The demographic and other baseline variables will be compared between study groups using descriptive statistics (means, standard deviations, proportions). For the primary analysis, a two sample two-sided test of proportions will be used to compare the difference in the incidence of PPD (major depression using the SCID) at 12 weeks post-randomization between the intervention and control groups. For secondary analyses, the statistical method to compare groups will depend on the distribution of the outcome variable in question. For binary variables (for example EPDS score > 12), a contingency table chi-square for a 2 × 2 table will be calculated and presented together with estimates for the relative risk, relative risk reduction, absolute risk reduction, and the number needed to treat. The corresponding 95 % confidence intervals for each estimated parameter will also be provided. Covariate variable adjustment will be achieved using logistic regression. For ordered categorical variables, a chi-square for trend will be calculated. Relative risks for each category versus a base category will be presented. Continuous variables with repeated measurement (such as anxiety) will be first analyzed using a single, repeated measures MANOVA consisting of group and time factors to test for the study’s overall intervention, time, or interaction effect. Following the detection of a significant effect, separate repeated measures 2-factor analyses of variance (RANOVA) with appropriate contrasts will show the nature of the effect within each outcome variable. Covariate variable adjustment will be achieved using analysis of covariance and linear regression. Finally, the relationship between the number of IPT sessions on PPD, and other study outcomes will be assessed to determine an effective dose response.

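### The EPDS is scored 0 to 30 and collected four times, but its only stated analysis is a cut at >12 tested by chi-square at 0.01; a baseline-adjusted score analysis should be prespecified beside it

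*Protocol article*

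**What the plan says.** Under *Depressive symptomatology* the protocol describes the scale: "Items are rated on a 4-point scale to produce a summative score ranging from 0 to 30". It then fixes how the outcome is read: the published cutoff of >12 "is used to examine depressive symptomatology at 12, 24, and 36 weeks post-randomization".

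Under *Statistical analysis plan – Primary analysis*, the same dichotomy is the worked example for binary outcomes: "For binary variables (for example EPDS score > 12), a contingency table chi-square for a 2 × 2 table will be calculated", with relative and absolute risk measures and the number needed to treat. Two sentences later it adds: "Covariate variable adjustment will be achieved using logistic regression". No covariate is named. Secondary outcomes are tested at two-sided 0.01. A repeated-measures route exists for continuous outcomes, but its example is anxiety; the EPDS score is not assigned to it.

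Table 1 lists the EPDS at baseline, 12, 24 and 36 weeks. The inclusion criteria require major depression on the SCID-I and set no EPDS threshold. Women who "self-identify as feeling down or depressed may also self-refer to the trial".

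*Justification for sample size* takes 70% v 50% still depressed, 80% power and alpha 0.05, giving 94 per group. It then says this size also gives power for a 20-point absolute reduction in secondary outcomes.

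**The concern.** The primary outcome is already a yes/no diagnosis. Cutting the only depressive-symptom scale at >12 makes it a second yes/no outcome, so the plan as written has no graded measure of how depressed women are. A woman who falls from 25 to 13 counts as unimproved, while one who moves from 13 to 12 counts as a success. The baseline score is collected but has no stated use in the comparison.

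Entry is by SCID and not by EPDS, so some women, most plausibly among the self-referred, may start at or below the cutoff and then count as non-symptomatic at follow-up without having changed.

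At stake is the sensitivity of the main symptom outcome at each follow-up. The primary SCID result is not affected.

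**Working it through.** **1. Inputs from the protocol.** Control 70% and intervention 50% (set for SCID depression; carrying them over to EPDS >12 is an assumption); 94 per group; alpha 0.05 for the primary and 0.01 for secondary outcomes. The protocol gives no EPDS standard deviation and no correlation between baseline and follow-up.

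**2. The plan's own figure.** With the pooled formula and no continuity correction,
n = [1.960·√(2·0.6·0.4) + 0.842·√(0.7·0.3 + 0.5·0.5)]² / 0.20² ≈ (1.358 + 0.571)² / 0.04 ≈ 93 per group, against 94 stated. It reproduces. Allowing for 20% loss, 188/0.8 = 235, against 240 planned.

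**3. Power of the stated EPDS test.** Power = Φ{[0.20 − z·√(2·0.6·0.4/94)] / √(0.46/94)} = Φ{[0.20 − z·0.0715] / 0.0700}.
- Alpha 0.05 (z = 1.960): 80.4%.
- Alpha 0.01 (z = 2.576): 59.0% (60.2% with 96 per group, that is 240 less 20%).
- For 80% power at 0.01 the chi-square would need 139 per group.

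**4. Score analysis if treatment shifts everyone.** Assume normal scores with equal SDs. Moving the share above the cutoff from 70% to 50% is a shift of z(0.70) − z(0.50) = 0.524 SD. With baseline correlation r, power ≈ Φ{0.524/√(1 − r²)·√(94/2) − 2.576}.

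| Analysis at alpha 0.01, 94 per group | Formula | Simulation |
|---|---|---|
| Chi-square on EPDS >12 | 59% | 57–60% |
| Score, unadjusted | 84.6% | 84% |
| Score, adjusted, r = 0.3 | 88.4% | 87–88% |
| Score, adjusted, r = 0.5 | 94.2% | 94% |

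Most of the gain comes from keeping the score and the rest from the baseline. Logistic regression on EPDS >12 adjusted for baseline reaches 60% (r = 0.3) to 68% (r = 0.5) in simulation, so the adjustment the protocol foresees closes little of the gap under this model.

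**5. Score analysis if treatment produces remission in a subset.** Keep the same 70% to 50% change, but let 2/7 of the treated women who would have scored above the cutoff (2/7 × 70% = 20 points) take scores from the control distribution below it, with the rest unchanged. For an even mix, half the 20 points comes from a shift (70% to 60%) and half from remission (60% to 50%). Simulated power at alpha 0.01, 94 per group:

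| Effect shape | Chi-square >12 | Score, unadjusted | Score, adjusted, r = 0.3 to 0.5 |
|---|---|---|---|
| Even mix | 57–58% | 62% | about 65–75% |
| Pure remission | 58–59% | 36–37% | about 39–45% |

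The chi-square hardly moves because the proportions are held fixed. The score analysis depends strongly on the shape of the effect.

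**6. Women who start at or below 12.** Their number cannot be derived from the protocol. Randomization spreads them evenly in expectation, so they dilute the difference in proportions without favouring either group.

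**The case against.** The cutoff has a stated basis. It is the published threshold, it matches the EPDS <13 recovery definition of the earlier treatment trials cited for the sample size, and it yields the number needed to treat. The public health partners' minimum worthwhile effect is an absolute difference in proportions, and the protocol frames benefit as recovery. A mean difference asks a different question. All of this stands, and it is why the cutoff result should stay.

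Four stronger readings are tempting and are not supported:

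- *That the same data would give about 88–94% power.* This holds only for a general shift with an assumed normal score and correlation. The documents give neither, and under pure remission the ranking reverses.
- *That the cut explains the low power.* The same chi-square has 80% power at 0.05 and 59% at 0.01, so the fall comes from the stricter level. That the sample-size section claims power for secondary outcomes from a calculation at 0.05 is a related but separate matter.
- *That baseline is ignored.* Logistic covariate adjustment is foreseen. Its covariates are unnamed, which a protocol article may leave to a fuller plan.
- *That women starting below the cutoff bias the comparison.* They dilute it.

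It can also be said that the continuous route is only illustrated by anxiety, so an EPDS score analysis is not barred and a fuller plan might contain one. That is fair, but this document fixes the cutoff as the way the outcome is examined, in two places that agree.

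**Conclusion.** The point holds as a cheap and worthwhile improvement to a secondary outcome. As written, the depressive-symptom outcome is dichotomised and tested with about 59% power at 0.01 for the 20-point effect the protocol has in mind, and the plan has no graded measure of depressive symptoms. A baseline-adjusted score analysis has 87–94% power if scores shift generally and r is 0.3–0.5, about 65–75% for an even mix of shift and remission, and 39–45% for pure remission. These figures assume that 70% v 50% carries over to EPDS >12 and are per time point; a model using all three follow-ups jointly was not evaluated. The case for the change is the added information from data already scheduled, with a power gain that is likely only if benefit is not confined to full remission in a subset.

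**What to change.** In *Depressive symptomatology* and in the analysis section, prespecify the EPDS score as an analysis of depressive symptomatology: the mean difference at 12, 24 and 36 weeks from a repeated-measures model adjusted for baseline EPDS and the stratification factors (province and self-reported history of depression). Keep EPDS >12 alongside it, with its risk difference and number needed to treat, and name baseline EPDS as a covariate in its adjusted analysis. State in advance which of the two carries the 0.01 test, so that the choice cannot follow the results.

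The cost is a sentence or two in each section and one more secondary analysis; no further data are needed. The drawback is that a mean difference is less directly tied to recovery than a proportion, which is why both should be reported.
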